##### Aim 1 Power Analysis:

We used the NCSS PASS [76] module for a two-level multilevel model with a continuous outcome and randomization at the cluster (i.e., health facility) level to compute the minimum detectable effect size estimates for hypotheses H1a-H1b. We assumed power of 0.80, α = 0.025 per comparison, and *N* = 2000 women from 40 facilities. We further assumed ICC = 0.16 based on our previous data [20, 77]. The minimum detectable standardized mean difference was *d* = 0.41, which is between small and medium effect size, suggesting the proposed primary analyses have sufficient power to detect small to medium effects [78].

##### Aim 2

We anticipate that the intervention will positively impact the intermediate outcomes in our conceptual model (Fig. 1), leading to an improvement in PCMC. We thus hypothesize that, following *CPIPE* exposure, intervention providers will have, higher mean scores on provider knowledge (H2a); self-efficacy (H2b); enabling environment (H2c); behavior (H2d), and lower mean scores on work-related psychological effects (stress, burnout, and bias) (H2e) relative to control providers. To test these hypotheses, we will fit three-level LMMs to each intermediate outcome, with fixed effects for study arm, time, and their interaction, random intercepts for facility ID to account for clustering of providers within health facilities, and random intercepts, random slopes, and their covariance for person ID to account for clustering of repeated measurements within providers. We will perform time-averaged comparisons of repeatedly measured post-baseline observations of the key intermediate outcomes across study arms to examine *CPIPE* intervention effects.

In secondary exploratory analyses, we will investigate whether the intermediate outcomes measured for providers at 6 months mediate the relationship between *CPIPE* intervention assignment and PCMC at 12 months. These analyses will be conducted using principles of structural equation modeling (SEM) and causal mediation methods [1]. We will explore whether *sex as a biological variable* differentially affects intervention effects on the provider-level primary analyses by adding a sex main effect and a sex-by-*CPIPE* assignment interaction term to the LMM models. Sex as a biological variable is not applicable to the mediation analyses due to the outcome applying to women only.

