### Randomization

Randomizing individual providers is not ideal because of a high potential for contamination within facilities and goal of changing facility culture. A cluster RCT design allows us to address threats to internal validity and account for natural clustering of providers within facilities [57]. Forty facilities will be randomized to intervention (*N* = 20) and control (*N* = 20), with arms stratified by country(10 intervention and 10 control facilities in each country). To reduce the risk of contamination due to interaction of providers within the same sub-counties and districts, randomization will be at the sub-county/district level such that control and intervention facilities are not in the same sub-county/district. The facility randomization will be done by a statistician not directly involved in the study. The intervention group will receive all strategies of the *CPIPE* intervention strategies over a period of 6 months after the baseline data collection. At the end of the 6-month implementation, we will collect midline data. Facilities will then be encouraged to continue with the intervention activities without involvement of the study for an additional 6 months, with final data collection at 12 months (endline). The control group will not receive the CPIPE intervention during the 12-month data collection period but will maintain their usual facility level activities. We plan to implement the intervention in the control sites after the endline data collection (assuming preliminary effectiveness). The protocol complies with the standard protocol items for cluster randomized trials. The study design, outcomes, and participant flow are summarized in Figs. 2 and 3.

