### Analysis plan

#### Data quality assurance, initial analyses, and missing data

We will use Redcap to perform real-time checks for data quality assurance [69, 70]. We will use frequency tables and measures of central tendency and variability for continuous variables to characterize the sample overall and by randomization group. If the two groups differ significantly at baseline on one or more covariates, we will use methods based on the Rubin causal model (e.g., propensity scores, double-robust estimation) to obtain the desired effect estimates under the counterfactual assumption of balanced groups [71, 72]. We will address incomplete data with direct maximum likelihood (ML) and multiple imputation (MI) [73] because they make the relatively mild assumption that incomplete data arise from a conditionally missing-at-random (MAR) mechanism [74]. Auxiliary variables will be included to help meet the MAR assumption [75]. The proposed analyses will be conducted using STATA. All program code and results will be documented extensively and archived to enable future review, transparency, and results reproducibility.

##### Aim 1

We hypothesize that mothers in the *CPIPE* intervention group will have higher mean PCMC scores than mothers in the control group at 6 months (H1a) and 12 months (H1b) after baseline. To test hypotheses H1a-H1b, in primary analyses we will fit two-level linear mixed models (LMM) to the PCMC score. Each of these two models will include a fixed effect for the study arm with random intercepts for facility ID to account for the clustering of women within health facilities. Because we will compare *CPIPE* to control at 6 months and then repeat the same comparison at 12 months, alpha (α) will be set at 0.05/2 = 0.025 for each of these two planned comparisons. In secondary analyses for Aim 1, we will extend the LMMs for PCMC to include effects for age and SES and their interactions with the intervention group indicator to explore whether the *CPIPE* intervention differentially benefits younger and lower SES women. Sex as a Biological Variable is not applicable: all participants will be biological females.

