##### Aim 2 Power Analysis

We used the NCSS PASS [76] module for three-level multilevel models with randomization at the cluster level to compute the minimum detectable effect size estimates for hypotheses H2a-H2e. We assumed power = 0.80, α = 0.05, and 2 post-baseline repeated assessments from *N* = 400 enrolled providers from 40 health facilities (*N* = 320 following 20% conservatively assumed attrition based on pilot data and our planned approach to reduce attrition) [52]. We conservatively assumed ICC = 0.15 based on our preliminary data [46, 67, 77]. Since the within-provider correlations are unknown, we varied them from *r* = .20 (small) to *r* = .80 (large). We computed the minimum detectable standardized mean difference *d* using the same inputs as listed above, yielding *d* = 0.40 to 0.44, which are between thresholds for small (0.20) and medium (0.50) standardized effects, suggesting the sufficient power to detect small to medium effects [78].

##### Aim 3

Improvements in PCMC are hypothesized to impact timely and appropriate care provision, care engagement, future health-seeking, and the physical and psychosocial health of women and their babies who receive care from those facilities, all of which positively influence maternal and neonatal outcomes. Recognizing that these distal outcomes are influenced by broader contextual factors and take longer to change, we propose an exploratory third aim to assess the impact of CPIPE on these outcomes during the study period and whether they are mediated by changes in PCMC. Given the exploratory nature of this aim, initial analyses will be descriptive, with frequency tables for all distal outcomes and measures of central tendency and variability for continuous distal variables at 6 and 12 months for intervention and control sites.

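### The detectable effects for Aims 1 and 2 rest on a normal reference although arm has at most 38 degrees of freedom; the t-based values are slightly larger (0.42, and 0.41 to 0.45)

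*Protocol article*

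**What the plan says.** The Aim 1 power analysis gives its inputs in full: "We assumed power of 0.80, α = 0.025 per comparison, and" 2000 "women from 40 facilities"; and "We further assumed ICC = 0.16 based on our previous data". The result follows: "The minimum detectable standardized mean difference was" *d* = 0.41.

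The analysis plan for Aim 1 compares arms at 6 and at 12 months in separate two-level linear mixed models, each with a fixed effect for arm and a random intercept for facility. It states that "alpha (α) will be set at 0.05/2 = 0.025 for each of these two planned comparisons".

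Under Randomization, 40 facilities are split 20 and 20, "with arms stratified by country(10 intervention and 10 control facilities in each country"). The same section says that the randomisation is done at sub-county or district level.

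The Aim 2 power analysis uses a three-level module with "randomization at the cluster level to compute the minimum detectable effect size estimates for hypotheses H2a-H2e". Its inputs are 80% power, alpha 0.05, 320 providers after attrition, 40 facilities, two post-baseline assessments, an ICC of 0.15 and within-provider correlations from 0.20 to 0.80. It reports detectable effects of 0.40 to 0.44.

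The paragraph on data quality and missing data contains the sentence "We will address incomplete data with direct maximum likelihood (ML) and multiple imputation (MI"). The article does not say whether the primary models use ML or REML, a z or a t reference, or any particular df method.

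**The concern.** Arm does not vary within a facility. However many women are interviewed, the information on the arm effect comes from 40 facility means, and the between-facility variance is estimated from those same 40 means. The reference distribution for the arm effect is therefore t with at most 40 − 2 = 38 df, not the normal. A power calculation on the normal scale uses a critical value that is too small and promises slightly more power than a correctly sized test delivers.

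The direct consequence is that alpha 0.025, 80% power and *d* = 0.41 do not hold together. A second consequence follows only under a condition: if the final tests also used an uncorrected normal reference, the 0.025 level set for each comparison might not be held.

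**Working it through.** **Inputs.** From the Aim 1 power analysis: 2000 women, 40 facilities (so 50 per facility on average), ICC 0.16, alpha 0.025, power 0.80. From Randomization: 20 facilities per arm. Two assumptions are added. Facilities are of equal size. The test is two-sided, which the article does not state but which is the reading that reproduces its figure.

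**Step 1: reproduce the Aim 1 figure.**
- Design effect = 1 + (50 − 1) × 0.16 = 8.84.
- SE of the standardised difference = √(4 × 8.84 / 2000) = 0.1330.
- Normal quantiles: 2.2414 for two-sided 0.025 and 0.8416 for 80% power.
- Detectable *d* = (2.2414 + 0.8416) × 0.1330 = 0.4099, the printed 0.41.
- A one-sided 0.025 test would give 0.373, which does not match.

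**Step 2: same inputs, t reference on 38 df.**
- The critical value rises from 2.2414 to 2.3337.
- Solving the non-central t power equation for 80% gives *d* = 0.424.
- Power at *d* = 0.41 is 77.0% instead of 80.0%.
- Change: 0.424 − 0.410 = 0.014, and 0.014 / 0.410 is about 3%.

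**Step 3: 38 df is an upper bound.** The setting section gives 8 sub-counties for the two Kenyan counties. Even read as 8 in each county, that is at most 16 for 20 Kenyan facilities, so some must share one. With at most 16 + 20 = 36 randomised units, df is at most 34. Changing the df alone, with the SE held at 0.1330, gives a detectable effect of 0.426 and power of 76.6% at 0.41.

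**Step 4: Aim 2.** 320 / 40 = 8 providers per facility with 2 assessments each, so 640 observations.
- Design effect = 1 + r + 2 × (8 − 1) × 0.15 = 3.1 + r, i.e. 3.3 at r = 0.20 and 3.9 at r = 0.80.
- SE = √(4 × 3.3 / 640) = 0.1436 and √(4 × 3.9 / 640) = 0.1561.
- Normal quantiles at two-sided 0.05 (1.960 + 0.842) give 0.402 and 0.437, the printed 0.40 to 0.44.
- t on 38 df gives 0.413 and 0.449, i.e. 0.41 to 0.45.

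**Step 5: size of an uncorrected z test at nominal 0.025 (conditional).** Suppose a z test were used and country explained none of the variance between facilities.
- REML-type variance: P(|t₃₈| > 2.2414) = 0.0309.
- ML variance: P(|t₃₈| > 2.2414 × √(38/40)) = 0.0352.
- 200,000 simulated null trials gave 0.0311 and 0.0353.
- If country explains 10% of facility-mean variance (an assumption), simulated size is 0.023 (REML) and 0.026 (ML). At 20% it is 0.016 and 0.018 to 0.019. Allocation is balanced within country, so a country difference left out of the model inflates the SE and makes the test conservative.

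**The case against.** A reader might infer that no small-sample correction is planned and that the primary tests therefore run at 0.031 to 0.035. The document does not support this. It specifies the model, the arm effect, the random intercept and alpha, and is silent on the estimator and df method. A condensed article commonly leaves those to the full protocol or the SAP, and neither is shown. Silence is not a plan to use z.

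A reader might also take the reference to direct maximum likelihood as the choice of ML over REML for the primary model. That sentence concerns incomplete data: it stands beside multiple imputation and is justified by the missing-at-random assumption. It does not settle the variance estimator, so the 0.035 figure cannot rest on it.

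Nor is the direction of any size error certain. Step 5 shows that even an uncorrected z test would be near or below 0.025 if country explained a tenth or more of the facility variance. Doubling the per-test figures to 0.062 to 0.070 for the pair gives only an upper bound, since both tests use the same facilities.

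Finally, the change in detectable effect is small. Raising the assumed ICC from 0.16 to 0.17 moves the normal-based value to 0.421, almost the same shift, and the description as lying between small and medium survives for both aims.

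These objections remove the claim of established type I error inflation and limit the weight of the rest. They do not remove the numerical point, which rests wholly on inputs the article prints: the stated figures match the normal reference, and the arm effect does not have one.

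**Conclusion.** The point stands as a minor error in two stated results. With the article's own inputs, the Aim 1 detectable effect is 0.42 rather than 0.41, with about 77% power at 0.41. The Aim 2 range is 0.41 to 0.45 rather than 0.40 to 0.44. These values assume two-sided tests, equal facility sizes and 38 df. They are lower bounds if several facilities share a randomised sub-county or district.

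Test size is a conditional matter only. About 0.031 (REML) to 0.035 (ML) per test would apply if an uncorrected z test were used and country explained no facility variance; the article establishes neither condition. The small-to-medium conclusion is unchanged.

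**What to change.** Restate the detectable effects as at least 0.42 for Aim 1 and at least 0.41 to 0.45 for Aim 2, computed with a t reference whose df reflect the units actually randomised. Specify, or confirm in the SAP if it already says so, that the arm effect is tested from REML fits with Kenward-Roger or Satterthwaite degrees of freedom for both aims, so that the test matches the restated power and the 0.025 level. The cost is one model option and two slightly less favourable figures. The sample size need not change on this account.

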#### Aim 2: Secondary outcomes to examine the mechanisms of impact of *CPIPE* on PCMC include

provider stress and burnout, bias awareness and mitigation, as well as provider knowledge, self-efficacy, and behaviors. Provider stress and burnout will be measured using the Cohen perceived stress scale [63] and the Shirom-Melamed Burnout measure [64], which we successfully used in Ghana and Kenya with demonstrated good psychometric properties [46, 65]. For implicit and explicit bias, we will use the Bias Awareness and Mitigation in Maternal Health scale [66] and vignettes, developed and tested in our prior research [67]. We will measure provider knowledge, self-efficacy, and behaviors related to stress, bias, and PCMC, using tools developed for the evaluation of the pilot study. Longitudinal provider surveys will be used to collect this data in all study arms at baseline, midline, and endline.

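### Aim 2 sex analysis: if baseline is an outcome row, as the random effects imply, the time-constant sex-by-arm term mixes in a pre-intervention wave and dilutes any sex difference in the CPIPE effect

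*Protocol article*

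**What the plan says.** All references are to the Protocol article.

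- **Analysis plan, Aim 2, model.** The plan fits "three-level LMMs to each intermediate outcome, with fixed effects for study arm, time, and their interaction". Besides a facility intercept it specifies "random intercepts, random slopes, and their covariance for person ID to account for clustering of repeated measurements within providers".
- **Analysis plan, Aim 2, intervention effect.** This is examined through "time-averaged comparisons of repeatedly measured post-baseline observations of the key intermediate outcomes across study arms", that is, averaged over midline (T2) and endline (T3).
- **Analysis plan, Aim 2, sex.** The plan explores whether sex "differentially affects intervention effects on the provider-level primary analyses by adding a sex main effect and a sex-by"-CPIPE "assignment interaction term to the LMM models". No sex-by-time or sex-by-arm-by-time term is listed.
- **Study outcomes, Aim 2.** "Longitudinal provider surveys will be used to collect this data in all study arms at baseline, midline, and endline". The Data collection section places T1 before the intervention starts at each facility.
- **Aim 2 Power Analysis.** The inputs are two post-baseline assessments, 320 providers after 20% attrition, 40 facilities, ICC 0.15 and a within-provider correlation of 0.20 to 0.80. The stated result is d = 0.40 to 0.44. No power is claimed for the sex analysis.

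**The concern.** A sex-by-arm term that does not involve time forces the sex difference in the arm contrast to be the same at every wave in the model. The effect it is meant to modify exists only after baseline. If T1 is one of the modelled waves, the coefficient is a weighted average of a pre-intervention contrast, where CPIPE can have had no effect, and the two post-baseline contrasts. Computing sex-specific post-baseline margins from the fitted model does not help, because their difference between arms is that same constant.

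Two things follow. A real sex difference in the CPIPE effect is shrunk towards zero, and any chance sex-by-arm imbalance at baseline is reported in part as effect modification. The analysis would then answer a different question from the one it names, and a null result would lean towards no sex difference.

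**Working it through.** **Step 1. The plan's own figure.** With m = 2 waves, n = 320/40 = 8 providers per facility, 20 facilities per arm and ICC = 0.15 (two-sided α = 0.05 assumed):

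d = (z₀.₉₇₅ + z₀.₈₀) × √[2f/(20·n·m)], with f = 1 + (m−1)r + m(n−1)·ICC.

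- r = 0.2: f = 1 + 0.2 + 2.1 = 3.3, so d = 2.80 × √(6.6/320) = 0.402.
- r = 0.8: f = 1 + 0.8 + 2.1 = 3.9, so d = 2.80 × √(7.8/320) = 0.437.

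This reproduces the stated 0.40 to 0.44, on two post-baseline waves.

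**Step 2. Does the model contain baseline?** Within facilities, two waves give a provider covariance matrix with 3 distinct elements (two variances and one covariance). The stated structure needs 4 parameters: intercept variance, slope variance, their covariance and a residual variance. These cannot all be estimated from T2 and T3 alone, so three waves are implied. This is an inference; the text does not state it.

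**Step 3. What the two-way term estimates over three waves.** With time-constant sex and sex-by-arm terms, the GLS coefficient weights the wave-specific sex-by-arm contrasts in proportion to V⁻¹1, where V is the provider covariance over waves t = 0, 1, 2. For intercept variance g₀₀, intercept-slope covariance g₀₁, slope variance g₁₁ and residual s², these weights simplify to:

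- weight on T1 = 1/3 + (g₀₁ + g₁₁)/(s² + 2g₁₁)
- weight on T2 = 1/3
- share recovered of a true pattern (0, δ, δ) = 2/3 − (g₀₁ + g₁₁)/(s² + 2g₁₁)

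The article gives no variance components, so those below are assumptions. The last column is the signal-to-noise ratio of the two-way term relative to the T2/T3-averaged contrast.

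| g₀₀ | s² | g₁₁ | correlation | T1 weight | share recovered | ratio |
|---|---|---|---|---|---|---|
| 0.5 | 0.5 | 0 | – | 0.333 | 0.667 | 0.71 |
| 0.5 | 0.5 | 0.05 | 0 | 0.417 | 0.583 | 0.64 |
| 0.5 | 0.5 | 0.10 | 0 | 0.476 | 0.524 | 0.60 |
| 0.5 | 0.5 | 0.05 | −0.6 | 0.259 | 0.741 | 0.78 |
| 0.8 | 0.2 | 0.05 | −0.6 | 0.100 | 0.900 | 0.91 |
| 0.8 | 0.2 | 0.10 | +0.3 | 0.795 | 0.205 | 0.24 |

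Worked example, second row: 2/3 − 0.05/(0.5 + 0.10) = 0.583. Fifth row: g₀₁ = −0.6 × √(0.8 × 0.05) = −0.12, so 2/3 + 0.07/0.30 = 0.900. The share exceeds two thirds exactly when g₀₁ is negative and larger in size than g₁₁. The T1 weight is also the fraction of any baseline sex-by-arm imbalance that enters the estimate.

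**Step 4. Attrition.** Take an exchangeable covariance with 20% of providers contributing baseline only. The information is 0.8/(1+2r) + 0.2 for T1 and 0.8/(1+2r) for each of T2 and T3. The share recovered is then about 60%, 57% and 55% at r = 0.2, 0.5 and 0.8.

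**Step 5. Simulation.** The set-up was 40 facilities × 10 providers, a true sex difference in effect of 0.40, 60% female (assumed), random intercepts only and 400 replicates. Three waves with the two-way term gave a mean of 0.275 (Monte Carlo SE 0.008), against 0.267 expected. The same term on T2 and T3 only gave 0.408 (Monte Carlo SE 0.008), which is full recovery.

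**The case against.** The strongest reply is that the article never says baseline is an outcome row. It speaks of post-baseline observations, and the power calculation uses two post-baseline assessments and reproduces on that basis. If only T2 and T3 are outcomes, nothing is diluted and the two-way term is adequate. That reading cannot be excluded, so the point must be conditional. It does not leave the text sound, however: on two waves the stated provider-level random structure cannot be estimated, so the Aim 2 paragraph needs an edit either way.

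A reader might also infer that the term recovers at most two thirds of a sex difference. The documents do not support that. Two thirds is the value for an exchangeable covariance with complete data, whereas the plan specifies random slopes with a covariance; under that structure the share can lie above or below two thirds. Similarly, a specific loss of power, or a fixed fraction of baseline imbalance entering, would rest on variance components and a sex mix that the article does not give.

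Finally, this is one clause of a condensed article about an exploratory analysis, and full term lists often sit in a statistical analysis plan. That limits the weight of the point. It does not remove it, because the article does name the terms to be added, and the terms named do not match the contrast they are said to modify.

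**Conclusion.** The point holds conditionally. If baseline is an outcome row, which the random-effects structure strongly implies but the text does not state, the sex-by-arm coefficient does not measure modification of the post-baseline contrast. It recovers two thirds of the difference under an exchangeable covariance with complete data, roughly 50% to 90% in most of the random-slope examples, and as little as 20% with a positive intercept-slope correlation. Attrition lowers the exchangeable figure to about 55% to 60%. In every case in the table the baseline wave carries positive weight, from 10% to 80%. If only T2 and T3 are modelled, there is no dilution. All sizes assume a sex difference that is equal at T2 and T3 and zero at T1, together with the variance components shown. H2a to H2e and the Aim 2 sample size are unaffected and the analysis is exploratory, so this is a point to consider.

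**What to change.** State in the Aim 2 analysis text which waves are outcome rows, then do one of the following.

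1. **Baseline is an outcome row.** Add sex, sex-by-time, sex-by-arm and sex-by-arm-by-time, and define effect modification as the sex-by-arm contrast averaged over T2 and T3, the same contrast as the main Aim 2 analysis.
2. **Only T2 and T3 are outcomes.** Enter the baseline value as a covariate and simplify the provider-level random structure so that it can be estimated from two waves. The sex-by-arm term as written then suffices.

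The first option costs a sentence, a few more fixed effects and a modestly larger standard error: 2% to 13% under an exchangeable covariance with r from 0.8 down to 0.2, and about 1% to 20% in the random-slope rows of the table. Neither option needs new data or a change in sample size.
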